## Anticipated Results

### Hypotheses and Planned Analyses

Some hypotheses were already roughly defined in winter 2015 and submitted to the KEK (see https://osf.io/ukbs5/). Here, we further detail those predictions and specify the statistical analyses that will be applied to test these hypotheses. The confirmatory analyses will be divided into two papers. Exploratory analyses will be published in additional papers, but these are not specified here.

First paper: the first confirmatory analysis will focus on the BFI. We will test the following hypotheses:
(1)BFI traits show high differential continuity over time (all *r* > 0.6). To test this prediction, we will compute bivariate Pearson correlations between trait scores at baseline and 6-month follow-up. We will provide both attenuated and disattenuated correlation coefficients corrected for scale unreliability.(2)BFI traits demonstrate substantial mean-level continuity (all *d* < 0.5). More specifically, we predict that only neuroticism will demonstrate modest mean-level change (0.2 < *d* > 0.5), while the other four traits will remain almost unaltered over time (all *d* < 0.2). These predictions will be tested with *t*-tests for paired samples by examining the differences in standardized mean-level change between baseline and 6-month follow-up.(3)Baseline BFI traits, specifically high neuroticism and low conscientiousness, substantially reduce (*d* > 0.5) the effectiveness of psychotherapy based on the BSI, GAF, and INK over the 6-month observation period. In order to test this prediction, we will compute GEE (121). These statistical models were introduced to fit regression analyses that account for within-subject correlation, which is an inherent part of longitudinal studies that rely on repeated outcome measures. Together with mixed models and random coefficient models, GEE represent the state of the art for longitudinal data analysis and are preferred to repeated measures ANOVA due to their superior psychometric properties (122, 123). The baseline BFI traits will be entered as the predictor variables and the repeated measures of the BSI, GAF, and INK successively as the outcome. The effect size of interest will be modeled as the interaction term between baseline personality and the time slope coefficient of the repeated outcomes, that is, the linear time trend for change in BSI, GAF, and INK. By simultaneously adjusting for the intercept, such a statistical modeling ensures that change in psychopathology over time is estimated independent of baseline impairment. These models will be conducted with and without adjustment for baseline diagnoses based on ICD-10.(4)Mean-level change in BFI traits is only weakly, if at all, correlated with change in psychopathological impairment over time (all *r* < 0.3). To test this hypothesis, we will compute individual change scores over time for all repeated measures by subtracting the baseline score from the follow-up score. The change scores of the BFI traits will then be correlated with the change scores of the BSI, GAF, and INK using Pearson correlation.

Second paper: the second confirmatory analysis will focus on the IIP and IMI-C. We will test the following hypotheses:
(1)Self-reports and informant ratings of interpersonal personality problems are only modestly correlated (all *r* < 0.3). To test this hypothesis, we will subject the IIP (self-report) and the IMI-C (informant rating) to a bivariate Pearson correlation analysis.(2)Both self-reported and informant-rated baseline personality problems according to the IIP and IMI-C substantially reduce (*d* > 0.5) the effectiveness of psychotherapy according to change in BSI, GAF, and INK from baseline to 6-month follow-up. As specified above with respect to the BFI, we will test these predictions by focusing on the interaction effect between baseline personality measures and the time slope coefficients of the psychopathology outcomes using a series of GEE analyses.(3)Self-other agreement in personality profiles relates stronger to the outcome of psychotherapy than either self-report (IIP) or informant rating (IMI-C). To test this hypothesis, we will first compute the index of profile agreement (*I*_pa_) between IIP and IMI-C as recommended by McCrae (124) and then compare the slope-interaction effect of the *I*_pa_ with the multivariable effects obtained for the IIP and the IMI-C domains based on the results of GEE as specified above. The difference between two effect sizes will be considered statistically significant if the 95% confidence intervals of their standardized regression coefficients do not overlap.(4)IIP and IMI-C have substantial incremental criterion validity (Δ*R*^2^ > 0.05) above and beyond each other in the prediction of the outcome of psychotherapy. This hypothesis will be tested by subjecting the change scores over time for BSI, GAF, and INK to a hierarchical linear regression analysis, where baseline IIP and IMI-C are entered in interchangeable hierarchical blocks as the predictor variables. In these models, the effect size of interest will be the amount of additional variance explained (Δ*R*^2^) accounted for by either IIP or IMI-C in the prediction of intraindividual change in BSI, GAF, and INK over time.

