Collection of data will include all German-speaking patients between 18 and 65 years who started psychotherapy at the KGI in Zurich dating back to September 2015 when FFM measures of personality were included in the standard test battery. Even though therapy is also offered to English speaking patients, restriction to German-speaking patients was made because assessments in English comprise different questionnaires. Data from a comprehensive assessment at outset of the psychotherapy will be used as baseline measures. After 6 months, all patients will be reassessed with a subset of these measures unless their therapy ended prior to that. These data will be used as the 6-month follow-up assessment. Originally, we planned to reassess patients after 12 months (second follow-up), but we now came to realize that this is not feasible because there are not enough patients who remain incessantly in therapy for so long. The 12-month follow-up will therefore not be executed. Based on power analyses, we intend to proceed sampling until we have approximately *n* = 100 6-month follow-up assessments. Because sample size calculation is intricate and not readily applicable for generalised estimating equations (GEE) analysis, we relied on the following three sources: firstly, we scrutinized various sample size recommendations for correlated data published in the methodological literature (84–86); secondly, we tested different sample size estimations based on repeated measure ANOVA calculated with G*Power (87); and thirdly, we considered the significance levels for varying effect sizes as obtained from applications of GEE in our previous work (14, 88–90). The final sample size of *n* = 100 was then estimated based on all these sources for an expected moderate effect size (0.3 < *d* > 0.5), a significance level of α = 0.05 and power (1 − β) > 0.8.

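### Hypotheses that trait change and correlations stay below a bound are judged by ordinary paired t-tests and bare Pearson coefficients, which cannot decide the bound, and the neuroticism range contradicts itself

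*Protocol article*

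**What the plan says.** All places are in the protocol article.

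- **Hypotheses and Planned Analyses, first paper, hypothesis (2).** Every Big Five Inventory (BFI) trait is predicted to change by d < 0.5, and the four traits other than neuroticism by d < 0.2. For the remaining trait, "neuroticism will demonstrate modest mean-level change (0.2 < *d* > 0.5". On the test: "These predictions will be tested with *t*-tests for paired samples by examining the differences in standardized mean-level change". The standardiser of d is not named.
- **Same section, first paper, hypothesis (4).** Trait change is expected to be at most weakly "correlated with change in psychopathological impairment over time (all *r* < 0.3". Change is follow-up minus baseline for every measure, and the analysis is a Pearson correlation with BSI, GAF and INK change.
- **Same section, second paper, hypothesis (1).** Self-report and informant rating are expected to be "only modestly correlated (all *r* < 0.3", again examined by Pearson correlation.
- **Study Site and Sampling Procedure.** The target is about 100 follow-up assessments, for an "expected moderate effect size (0.3 < *d* > 0.5", with "a significance level of α = 0.05 and power (1 − β) > 0.8".

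The Summary and Conclusion presents the analyses as exactly prespecified. The only explicit decision rule based on confidence intervals is in second-paper hypothesis (3), for a different question.

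**The concern.** A prediction that an effect lies below a bound is supported when the data exclude values beyond the bound. A test of zero change does not do that. A non-significant result is compatible with a change above 0.2, and a significant one is compatible with a real change below 0.2. Reading the point estimate against the bound instead ignores sampling error.

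The bounds are also printed without absolute values. This matters because GAF rises as symptoms fall, so the same clinical association carries opposite signs for GAF and for BSI or INK. The neuroticism range, read literally, cannot hold together with the limit stated one sentence before it.

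Trait stability and the link between trait change and symptom change are two of the five aims in the Abstract. A reader of the results could not tell whether confirmed means a p-value above 0.05, an estimate under the bound, or a bound excluded with confidence.

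**Working it through.** **Inputs from the article:** n = 100 pairs, α = 0.05, bounds 0.2, 0.5 and 0.3. **Assumptions:** two-sided testing; d scaled either by the SD of change or by the baseline SD (equal SDs at both times); retest r of 0.6, 0.7 or 0.8 in the second case.

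**1. The plan's own figure.** By the noncentral t distribution, a paired t-test with 100 pairs has power 0.844 at d = 0.3, 0.977 at 0.4 and 0.999 at 0.5; 80% power at d = 0.3 needs 90 pairs. Power above 0.8 therefore holds if the planning range is read as 0.3 to 0.5. The article calls n approximate and draws on three sources, so the sample size is not in dispute. That power is for detecting a difference from zero, however, not for showing that a change is below a bound.

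**2. Paired t-test against the 0.2 bound.**
- SE of d: √(1/100) = 0.100 on the SD-of-change scale; √(2(1 − r)/100) = 0.089, 0.077, 0.063 on the baseline-SD scale.
- Smallest significant d = 1.984 × SE.
- Power of the confidence-interval rule (90% CI within ±0.2) at true d = 0: 2Φ(0.2/SE − 1.645) − 1. For example, with SE 0.100: 2Φ(0.355) − 1 = 0.28.

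| Scale of d | Smallest significant d | Significant at true d = 0.15 (bound met) | Not significant at true d = 0.25 (bound broken) | 90% CI within ±0.2 at true d = 0 |
|---|---|---|---|---|
| SD of change | 0.198 | 32% | 30% | 28% |
| Baseline SD, retest 0.6 | 0.177 | 38% | 21% | 45% |
| Baseline SD, retest 0.7 | 0.154 | 48% | 11% | 65% |
| Baseline SD, retest 0.8 | 0.125 | 65% | 2.5% | 87% |

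For the ±0.5 bound at true d = 0, the confidence-interval rule has power above 99% on either scale.

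**3. Point-estimate reading of the 0.2 bound.** P(observed d < 0.2 given true d) = Φ((0.2 − d)/SE). At d = 0.2 this is 50%. At d = 0.25 it is Φ(−0.5) = 31% on the SD-of-change scale and 29%, 26% and 22% on the baseline-SD scale.

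**4. Correlations.** Fisher z, SE = 1/√97 = 0.1015.
- Observed r = 0.29: z = 0.2986 ± 1.96 × 0.1015, giving a 95% CI of 0.10 to 0.46. The estimate meets the bound, while the interval reaches well beyond it.
- For the 90% CI to lie within ±0.3, |r| must be below tanh(0.3095 − 1.645 × 0.1015) = tanh(0.1425) ≈ 0.14.
- Under that rule a single correlation is confirmed in 84% at true r = 0, 65% at 0.1 and 28% at 0.2.

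**5. The printed ranges.** 0.2 < d > 0.5 states d > 0.2 and d > 0.5, which together mean d > 0.5. This contradicts the limit of 0.5 for all traits. The planning range has the same form, 0.3 < d > 0.5.

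**The case against.** **No zero null is written for the correlations.** Correct. For the r hypotheses the text only says that coefficients are computed, so the defect there is the missing link between estimate, uncertainty and bound. For hypothesis (2) the zero null is inferred from the ordinary paired t-test, although the sentence also mentions the standardised change.

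**The t-test figures depend on an unstated scale.** Also correct. On the SD-of-change scale the significance limit of 0.198 practically equals the 0.2 bound, so the p-value and the point estimate agree. Even then the rule passes half the time when the true d sits exactly on the bound. The missing standardiser is part of the problem.

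**The sign and the range are visible slips.** Probably so. A reader might infer that r = −0.6 would be counted as confirmation, but the prose describes the correlations as weak or absent and the four traits as practically unchanged, so magnitude is meant. The neuroticism range almost certainly intends 0.2 to 0.5. Both still need correcting where the threshold is itself the prediction.

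**Stronger readings that the article does not support.**
- First-paper hypothesis (1) does not share the upper-bound fault: r > 0.6 is a lower bound.
- Requiring every bound to hold is not an error. It makes confirmation harder: if all 15 true correlations were 0.20, all estimates would fall below 0.30 in 0.854^15 = 9% of studies under independence (21% in a simulation with assumed intercorrelations). That is a strict choice, and it does not inflate false confirmation.
- A low change correlation is not shown to be built in by unreliable change scores. That depends on reliabilities the article does not give, and Caveats and Potential Pitfalls warns of content overlap, which would push the association upward.

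**Conclusion.** The point stands for first-paper hypotheses (2) and (4) and second-paper hypothesis (1). The test named for hypothesis (2) cannot decide its 0.2 bound: at n = 100 it is significant in 32% to 65% of studies at a true d of 0.15, and non-significant in up to 30% at 0.25, depending on the standardiser and an assumed retest r of 0.6 to 0.8. The 0.5 bound is much less exposed, because 100 pairs can confirm it easily under a suitable rule. The r < 0.3 hypotheses have no rule that takes account of sampling error. The neuroticism range contradicts the bound stated just before it.

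This is more than detail left to an analysis plan, since the article itself fixes the test and the thresholds and describes them as exact.

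**What to change.** Before the data are analysed, in a dated correction or addendum:

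- Write the bounds as |d| and |r|, and name the standardiser of d.
- Correct the ranges to 0.2 < |d| < 0.5 for neuroticism (Hypotheses and Planned Analyses) and 0.3 < d < 0.5 for planning (Study Site and Sampling Procedure).
- Decide hypothesis (2) by whether the 90% CI of d lies within ±0.5 (all traits) or ±0.2 (the four others).
- Decide the r < 0.3 hypotheses by whether the 90% CI of r lies within ±0.3.
- Call a result inconclusive when the interval crosses a bound.
- Report a verdict per trait or per correlation alongside any verdict on all of them together.
- Say how the lower end of the neuroticism range is judged. If the whole 90% CI had to fit between 0.2 and 0.5, its width of about 2 × 1.645 × 0.100 = 0.33 on the SD-of-change scale would exceed the 0.30 available. With the baseline SD and retest 0.7 it is about 2 × 1.645 × 0.077 = 0.25.

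The cost is wording; no new data are needed. The downside should be stated openly: many verdicts will be inconclusive. Even at a true d of 0, the ±0.2 bound is confirmed per trait in only 28% (SD of change) or 45%, 65% and 87% (baseline SD, retest 0.6, 0.7, 0.8). For 80% power per trait, 215 pairs would be needed on the first scale and 172, 129 or 86 on the second. An observed |r| must be below about 0.14 to confirm |r| < 0.3.

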## Stepwise Procedures

This observational naturalistic study was approved by the Cantonal Ethics Committee of Zurich (KEK) in December 2015 (reference number 2015-0601). The project is financially supported by a grant from the OPO Foundation (reference number 2016-0038) awarded in June 2016 to [name]. The funder will have no bearing on the conduct, analysis, and interpretation of the data and the decision to submit a manuscript for publication. As stated above, all German-speaking patients starting psychotherapy at KGI in September 2015 and afterward will be included in the dataset. At present a total of *n* = 58 baseline and *n* = 6 follow-up measurements have been completed (effective October 2016). To achieve the projected sample size of *n* = 100 at 6-month follow-up, data collection will presumably continue until autumn 2017. Data analysis and manuscript draft will start immediately once the projected sample size has been reached. Study results are intended to be published in leading journals of clinical psychology, psychopathology, and psychotherapy.

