### Caveats and Potential Pitfalls

We have stressed that clinical trials in psychotherapy and psychopharmacology commonly have poor external validity, that is, the efficacy of treatments for mental disorders as estimated in the laboratory under controlled conditions using selective samples only poorly corresponds to real-world effectiveness in unselected naturalistic samples (47, 48). On the other hand, clinical trials have considerably higher internal validity than observational studies, which is why they are considered the gold standard for the estimation of causal effects. That holds particularly true when the main objective is to evaluate the efficacy of a given intervention. Observational studies are merely correlational, as interventions cannot be randomly assigned to participants. Therefore, they do not allow for strict causal conclusions, although sophisticated statistical techniques such as propensity score matching can approximate the internal validity of observational designs to that of randomized experiments (125). However, as we are mainly interested in the longitudinal covariance between personality and psychopathology and in the stability of personality, but not on the efficacy of psychotherapy as an intervention *per se*, that potential limitation is not at issue. That is, we are not interested in testing the efficacy of an intervention, but rather in evaluating possible mechanisms operating within that particular intervention. We will therefore not apply propensity score matching, as we do not compare psychotherapy users with untreated patients or other treatment modalities. A bias that needs to be addressed in such a study is the content overlap between personality and psychopathology, in particular that between neuroticism and depression (126), as that bias might artificially inflate the association between these constructs. To solve that problem, we will apply outcomes such as the GAF and the INK that have no content overlap with neuroticism. Moreover, we will also use alternative measures of personality such as the circumplex model of personality problems, which will be assessed based on both self-report and informant rating. Finally, though we consider the heterogeneity of this representative sample a particular strength, one might also argue that we compare apples to oranges. That argument holds particularly true with respect to interindividual differences in baseline impairment. As detailed above, we will resolve that issue by applying statistical models that estimate the change in psychopathology over time while holding baseline impairment constant. In order to additionally control for distinct baseline psychopathology, we will also include a patient’s primary diagnosis as a covariate.

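### Two hypotheses say that traits reduce the effectiveness of psychotherapy, but the trait-by-time term in a treated-only cohort is prognostic and cannot isolate a smaller treatment effect

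*Protocol article*

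**What the plan says.** All references are to the Protocol article.

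- **Hypotheses and Planned Analyses, first paper, hypothesis (3).** Baseline traits, specifically high neuroticism and low conscientiousness, are predicted to lower "the effectiveness of psychotherapy based on the BSI, GAF, and INK over the 6-month observation period". The verb is causal and carries a size: "substantially reduce (*d* > 0.5").
- **Same section, second paper, hypothesis (2).** Self-reported and informant-rated interpersonal problems (IIP, IMI-C) are predicted, with the same verb and size, to lower "the effectiveness of psychotherapy according to change in BSI, GAF, and INK from baseline to 6-month follow-up".
- **The test for both.** "The effect size of interest will be modeled as the interaction term between baseline personality and the time slope coefficient of the repeated outcomes", fitted by GEE. The first-paper models are run with and without adjustment for ICD-10 diagnosis.
- **Stepwise Procedures, the cohort.** "all German-speaking patients starting psychotherapy at KGI in September 2015 and afterward will be included in the dataset".
- **Caveats and Potential Pitfalls, the comparator.** "we do not compare psychotherapy users with untreated patients or other treatment modalities".
- **Caveats and Potential Pitfalls, the limitation.** The section concedes that observational studies are correlational and do not support strict causal conclusions. It then says that the authors' interest is in longitudinal covariance and trait stability, "but not on the efficacy of psychotherapy as an intervention *per se*, that potential limitation is not at issue". The next sentence gives the aim as examining mechanisms at work inside the therapy.

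**The concern.** Saying that a trait reduces the effectiveness of a treatment is a claim of effect modification: the difference between treated and untreated course is smaller in people with more of the trait. The planned analysis never observes the untreated course. It shows only whether patients with more of the trait improve less while in therapy. They might do so because therapy works less well for them, because their problems would have resolved more slowly in any case, or both.

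The wording matters more here than in an ordinary observational paper, because the article presents its hypotheses as strictly confirmatory and fixed in advance. The prespecified sentence is the one that a significant interaction would be taken to confirm. Confirming a statement about treatment effectiveness is a different conclusion from confirming that a trait predicts less improvement, and only the second is available from these data.

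**Working it through.** The planned sample size does not bear on this point, and no stated figure is in dispute. The question is what the planned coefficient identifies.

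**1. The planned term.** Let x be the standardised baseline trait, scored so that higher means more of the problem, and let Y be an outcome on which higher is worse (the sign is reversed for GAF). Write the six-month change as

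- without this therapy: a + n·x
- added by therapy: g + t·x

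Here n is the trait's effect on the course that would have occurred anyway, and t is its effect on treatment benefit. A positive t means less benefit for high scorers. Everyone in the cohort is treated, so

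E(change | x) = (a + g) + (n + t)·x.

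With two complete waves, the GEE trait × time coefficient equals the least-squares slope of change on the trait, which is n + t. The hypotheses as worded concern t. Nothing in the data separates t from n.

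**2. At the predicted size.** Read the predicted 0.5 as n + t = 0.5. It is met by n = 0, t = 0.5 (therapy works less well); by n = 0.5, t = 0 (therapy works equally well); and by any n above 0.5 with t negative (therapy works better for high scorers).

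**3. Numerical check.** The coefficients below are assumed for illustration, not taken from the document. Each scenario has n + t = 0.25. The treated-only columns come from 4,000 simulated cohorts of 100 patients, tested two-sided at 0.05. The last column comes from one simulated data set of 400,000 that includes an untreated group.

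| Scenario | n | t | Treated-only trait × time | Rejection rate | Trait × time × treatment, with untreated group |
|---|---|---|---|---|---|
| A: slower natural course only | 0.25 | 0 | 0.251 | 0.933 | 0.00 |
| B: smaller treatment effect only | 0 | 0.25 | 0.251 | 0.931 | 0.248 |
| C: half each | 0.125 | 0.125 | 0.250 | 0.929 | 0.125 |
| D: worse course, larger treatment benefit | 0.40 | −0.15 | 0.250 | 0.930 | −0.157 |

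The treated-only analysis gives the same answer in all four rows, including D, where the trait increases treatment benefit. The last column recovers t apart from simulation error.

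**4. Whether the planned adjustments help.** Adjusting for the intercept accounts for differences in baseline level, and adjusting for ICD-10 diagnosis accounts for differences in case mix. Neither supplies the course that the same patients would have had without therapy.

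**5. Whether n different from zero is plausible on the document's own account.** The Introduction, under the heading on personality for public mental health and psychotherapy, reports that traits still predict later psychopathology to a substantial degree after adjustment for baseline impairment. It cites this as general longitudinal evidence, before turning to psychotherapy. It then names the course of psychopathology and the efficacy of psychotherapy as two separate things that personality affects. The planned term merges the two.

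**The case against.** The strongest reply is that the hypotheses say what they mean by effectiveness. The second-paper version ties it to "the effectiveness of psychotherapy according to change in BSI, GAF, and INK from baseline to 6-month follow-up", and the first-paper version defines its effect size as an interaction with the time trend. A careful reader knows that observed change is being modelled. No hypothesis claims benefit over no treatment, and the Abstract and hypotheses (3) and (4) of the second paper already use the neutral term outcome. This stands in part: it makes the problem one of over-reaching wording and leaves the analysis itself intact. It does not remove the problem, because the verb is causal and its object is the effect of therapy. Elsewhere (What This Project Adds to the Literature) the article uses effectiveness for the real-world counterpart of efficacy, which is a treatment effect.

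A reader might infer that the hypotheses and the caveat flatly contradict each other. The documents do not support that. Disclaiming interest in whether psychotherapy works is compatible with asking who improves less during it.

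A reader might also infer that the caveat dismisses the natural-course problem. It does not mention natural course. What it sets aside is the general lack of strict causal conclusions, and it does so after conceding that the design is correlational and stating openly that there is no untreated comparison.

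Finally, how the results papers will be worded is not fixed in the article, so a misreported finding is a risk and not a certainty. No numerical result would change.

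**Conclusion.** The point holds in a limited form. For hypothesis (3) of the first paper and hypothesis (2) of the second, the planned term supports a prognostic statement (less improvement during therapy in patients with more of the trait) and not a statement that the trait makes therapy less effective. The argument that "that potential limitation is not at issue" is sound for trait stability, self-informant agreement and plain prediction of change. It does not extend to these two hypotheses or to the stated interest in mechanisms within the intervention.

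The size is one of interpretation: any observed interaction, including one of 0.5, is compatible with a treatment-effect difference of the same size, of zero, or of the opposite sign, and a larger sample would not narrow this. The conclusion rests on the cohort being entirely treated, which the article states, and on the additive decomposition above. The simulation coefficients are assumptions, but the equality of the treated-only estimates depends only on their sum. Severity: minor.

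**What to change.** 1. Restate both hypotheses prognostically: the trait (first paper), or the self-reported or informant-rated interpersonal problem (second paper), *predicts less improvement in BSI, GAF and INK during 6 months of psychotherapy*. This matches the outcome wording already used in the Abstract and in hypotheses (3) and (4) of the second paper.
2. In Caveats and Potential Pitfalls, qualify the sentence that sets the limitation aside. Keep it for trait stability, self-informant agreement and prediction of change. Add that the trait × time effect is prognostic, does not estimate a difference in treatment effect, and cannot by itself identify mechanisms of the therapy.

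No untreated group is needed for the restated hypotheses. The cost is a few sentences and a slightly less strong conclusion. Model, data, sample size and test are unchanged.
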